**Methods::**

This randomized, controlled, assessor-blinded, 2-armed, parallel, multicenter clinical trial will analyze a total of 50 subjects, including 25 each for the test group and the active control group. Subjects will be randomly allocated to the test group (performing resource mindfulness) and the control group (performing stress mindfulness) in a 1:1 ratio. The clinical trial consists of 3 stages. The first and third stages are stable states. The second stage is divided into the test and active comparator groups. Quantitative EEG (qEEG) measurements at stages 1 and 3 will be recorded for 10 minutes; measurements at stage 2 will be recorded for 20 minutes with the eyes closed. The 24-hour Holter Monitoring and heart rate variability will be evaluated at each stage. Before the beginning of stage 3, subjects will complete the questionnaires. The primary outcome will be analyzed by independent *t* tests of both groups.

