### Trial design and study setting

2.2

This clinical research will be conducted with subjects who provide voluntary consent and will be reviewed according to the inclusion or exclusion criteria of the clinical trial plan. Selected subjects will be assigned randomly into the test or active comparator group, according to precompleted random templates. The study design is as follows. This randomized, controlled, single-blinded, 2-armed, parallel, clinical trial will collect a total of 50 subjects, including 25 each for the test and active comparator groups. The subjects will be randomly allocated to a test group performing resource mindfulness (RM), and a control group performing stress mindfulness (SM), at a 1:1 ratio. The clinical trial consists of 3 stages, 20 minutes each (60 minutes total). The first and third stages are stable states. The second stage is divided into the test group and the active comparator group. The test group subjects will practice RM meditation and the active comparator group subjects will practice SM meditation. RM or SM meditation guide scripts will follow the M&L Psychotherapy Manual and the meditation guide will be directed by a professional practitioner trained by the M&L psychotherapist course. At stages 1 and 3, qEEG measurements will be taken for 10 minutes (5 minutes with eyes open and 5 minutes with eyes closed) from 5 minutes after the beginning of the stage. In the second stage, the qEEG measurements will be taken for 20 minutes, with eyes closed. The 24-hour Holter monitoring^[20]^ will be performed through stages 1, 2, and 3; HRV will be evaluated during each stage. The blood pressure and pulse will be measured before and after the second stage. All processes related with clinical trial including plans for collecting, assessing, reporting, and managing solicited and spontaneously reported adverse events and other unintended effects of trial interventions or trial conduct will be monitored and modified primarily by researcher director and peer researchers to ensure participants’ safety and research design's accuracy. A diagram and the time schedule of this study are shown in Table 1 and Fig. 1.

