#### Randomization with Excel 2016

2.7.1

The randomization number allocated according to the assigned tables generated will be managed by the clinical trial manager and sent to each hospital. Consent will be obtained by a Korean Medicine doctor. If the participant voluntarily signs informed consent and meets the inclusion criteria, the clinical research coordinator (CRC) will sequentially allocate the participant to the treatment or control group according to the random number and record the subject identification code on the case recording sheet and the assignment table.

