### Blinding: single blind

2.8

Because of the study design, practitioners cannot be blinded. Only the participants will be blind. The assessor will be instructed to refrain from talking about the treatment to maintain blinding.

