#### qEEG

2.10.1

The EEG of the subjects will be measured in a comfortable, quiet, cool room, wearing an electro-cap (Electro-cap; Mitsar, Russia) with 21 surface electrodes placed in an international 10/20 system, for 5 minutes each in open-eye and closed-eye states. All electrode impedance will be less than 5 KΩ, based on the method of Ferree et al.^[31]^ The reference electrode will be located between Fz and Cz; the amplifier will be a Mitsar-EEG 201 machine (Mitsar, Russia). Artifacts of the recorded EEG, modified automatically, will be manually removed by the qEEG expert for a reliability measurement of 0.9 or better. Spectral analysis, coherence, and Low Resolution Brain Electromagnetic Tomography analysis will be performed with WinEEG for records with artifact-free EEG segments >2 minutes and split-half reliability >95%. Spectral analysis will use linked-ears reference montage and local average (Laplacian) montage.^[32,33]^ Linked-ears reference montage will be used as a general criterion; local average (Laplacian) montage can emphasize localized areas and minimize the overall effect of drugs on the brain.^[34]^ The absolute power and relative power will be calculated as delta (0.5–4 Hz), theta (4–8 Hz), alpha (8–12 Hz), and beta (12–20 Hz), respectively, using the absolute power and relative power. Neuro-guide will be used as the basis for all analyses; EEG analysis will be conducted by BCN, an expert KMD. In addition, the EEG results will be analyzed by KMD and CP after mentoring by a neuro feedback supervisor (BCN) and biofeedback specialist on Applied Psychophysiology in the United States.

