### Data management and quality control

2.12

The CRC will collect data on a paper CRF. Records including medical records, questionnaires, consent forms, and other clinical trial relevant papers will be stored at each site in a locked cabinet or a password-protected computer that can be accessed only by an authorized individual and kept confidential, even when the results of the clinical trial are published. However, quester, monitor, and inspectors related to this clinical trial can view each subject's records for the purpose of monitoring and checking this clinical trial and management of the subject's progress. Additionally, all documents related to this clinical trial, such as case histories, will be recorded and distinguished by using each subject's identification code (typically the subject's initials), but not by using any subject's name. After completion of the outcome report, the research will be kept for 5 years from the end of the clinical trial.

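### The abstract calls the trial assessor-blinded, section 2.8 blinds participants only, and nothing stated masks the manual editing of the qEEG, one of two primary measures.

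*Protocol article*

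**What the plan says.** Three places in the protocol article describe the blinding.

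- Abstract, Methods: "This randomized, controlled, assessor-blinded, 2-armed, parallel, multicenter clinical trial".
- Section 2.2: "This randomized, controlled, single-blinded, 2-armed, parallel, clinical trial will collect a total of 50 subjects". The blinded party is not named.
- Section 2.8, headed single blind, says practitioners cannot be blinded and then "Only the participants will be blind". It continues: "The assessor will be instructed to refrain from talking about the treatment to maintain blinding".

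Section 2.10 lists two measures under the primary heading: qEEG (2.10.1) and 24-hour Holter monitoring with HRV (2.10.2). In 2.10.1, after an automatic step, artifacts "will be manually removed by the qEEG expert for a reliability measurement of 0.9 or better". Records go forward to analysis if they hold more than 2 minutes of artifact-free EEG and have split-half reliability above 95%. The EEG analysis is then assigned to clinical staff, and their masking is not mentioned. The abstract says the primary outcome is compared between the groups by independent t tests.

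Sections 2.9.5 and 2.9.6 describe what participants do: one arm recalls a positive inner resource, the other recalls a stressful situation.

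**The concern.** Assessor blinding is a property that readers and evidence reviewers use to judge detection bias. Here the summary claims it, and the section that governs blinding restricts blinding to participants. The request that the assessor not talk does not close the gap. It protects the participant from what the assessor might disclose, and it leaves open what the assessor knows.

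At stake is a primary measure with a human judgement in it. Deciding which stretches of EEG are artifact determines which data enter the spectra. If the editor knows the arm and edits the two arms differently, even unintentionally, the difference passes straight into the between-group comparison. The trial could then be reported as assessor-blinded although its own blinding section says otherwise.

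**Working it through.** No figure in the protocol depends on blinding, so the main check sets the texts side by side.

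**Step 1. Can the three blinding statements hold together?**

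| Place | Participants | Assessor |
|---|---|---|
| Abstract, Methods | not stated | blind |
| Section 2.2 | one unnamed party is blind | one unnamed party is blind |
| Section 2.8 | blind | not blind (blinding limited to participants) |

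Section 2.2 fits either of the others, so it cannot settle the matter. The abstract and 2.8 contradict each other, and no other section resolves it.

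**Step 2. Does the second sentence of 2.8 amount to assessor blinding?** No. An assessor who has to be told not to discuss the treatment is one who might know it.

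**Step 3. Is there a judgement in a primary measure?** Yes, for qEEG, through the manual artifact removal in 2.10.1. For Holter/HRV, section 2.10.2 describes no manual editing, so this argument does not extend to that measure.

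**Step 4. Do the stated safeguards cover the gap?** The automatic step comes first and leaves less to the expert. The criteria (reliability 0.9 or better, more than 2 minutes artifact-free, split-half above 95%) test whether a record agrees with itself and is long enough. A record can pass all of them while the rule for what was cut differs between arms. They limit discretion and say nothing about its direction by arm.

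**Step 5. How sensitive is the test to an editing shift? Illustration only.** The protocol gives no size for such a shift; the values of d below are assumptions with no source in it. Further assumptions are no true effect, a two-sided 5% t test, a shift always in the same direction, and 50 × (1 − 0.10) = 45 evaluable, split 22 and 23.

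- Noncentrality: λ = d × √(22 × 23 / 45) = d × √11.244 = 3.353 d
- Critical value on 43 degrees of freedom: 2.017
- Rejection probability: P(|T| > 2.017), with T noncentral t with parameter λ

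| Shift d (SD) | λ | Rejection, 22/23 | Rejection, 25/25 |
|---|---|---|---|
| 0 | 0 | 0.050 | 0.050 |
| 0.2 | 0.671 | 0.101 | 0.107 |
| 0.3 | 1.006 | 0.166 | 0.180 |
| 0.5 | 1.677 | 0.374 | 0.410 |

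The table shows only that a modest consistent shift would matter if it occurred. It is no evidence that it would occur.

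**The case against.** The strongest reply is that this is a condensed article. Section 2.15 cites a full protocol, version 2.3, and how EEG files are labelled for the reader is the kind of detail left to that document. This stands: the absence of a file-coding procedure is not by itself an error. It does not remove the contradiction, because both conflicting statements are in the article.

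A reader might also infer stronger points that the document does not support.

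- *That nobody on the measurement path is masked.* Section 2.10.1 does not say whether the qEEG expert knows the arm. Lack of masking is inferred from 2.8, not stated for that person.
- *That the coordinator writes the arm on the case report form.* Section 2.7.1 does say "the clinical research coordinator (CRC) will sequentially allocate the participant to the treatment or control group according to the random number", and section 2.12 says "The CRC will collect data on a paper CRF", so one role both allocates and collects. But what goes on the case recording sheet is the subject identification code, whose format in 2.9.2 carries no arm. Collecting forms is also not shown to be a judgement about instrument recordings. The trial manager already manages the randomization numbers, and allocation already follows consent and eligibility.
- *That detection bias in the primary result is established.* The automatic step and the thresholds reduce the room for it, Holter/HRV is also primary, and the size of any bias is unknown.

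On participant blinding, both arms practise mindfulness meditation guided from the same manual, so participants could well be unaware which arm is the test arm. That stands. They do know the content they recall, so an unqualified statement that they are blind claims too much.

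**Conclusion.** The contradiction is certain from the text: the abstract claims assessor blinding, section 2.8 limits blinding to participants, and section 2.2 does not decide between them. Followed as 2.8 is written, the manually edited qEEG has no stated masking of its editor.

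The consequence is a risk that is unprotected, not demonstrated. It rests on two readings: that the word only in 2.8 means what it says, and that manual artifact removal leaves some discretion after the automatic step and the thresholds. The size of any bias is unknown, and the illustrated error rates of 10% to 37% depend entirely on assumed shifts of 0.2 to 0.5 SD. The case for correction rests on the contradiction and on qEEG being a primary measure, and does not need those figures.

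**What to change.** 1. In section 2.8, state that the qEEG editor, the qEEG analysts and the Holter/HRV analyst work on files coded without arm, and that edited records are locked before the code is broken.
2. Make the abstract, section 2.2 and section 2.8 agree, naming in each who is blind. If the masking in item 1 is not done, remove assessor-blinded from the abstract.
3. Describe participants as unaware of the study hypothesis, or of which arm is the test arm, since they know what they are asked to recall.

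The cost is a paragraph of text and minor file handling. The relabelling and the code must be held by someone other than the editor, so it is not entirely free. No extra participant procedure is needed. Section 3.1 reports that recruitment has begun, but coding can still be applied to stored recordings that have not yet been edited.

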### Intervention

2.9

#### Study schedule

2.9.1

The study schedule is presented in Table 1. The study will include a screening phase, as a clinical step, the phase of before-meditation measurement, the phase of resource or stress mindfulness meditation, and the phase of postmeditation measurement. The participants will be recruited from the Wonkwang University Medical School Sanbon Hospital.

#### Screening phase

2.9.2

At the screening phase, before conducting this clinical trial, the Korean oriental medical doctor (KMD) will explain to the subjects the contents of the “Instructions for obtaining subject consent” and confirm that the subject understands the contents, and that KMD must receive written permission that each subject is participating in the clinical trial of their own free will. And then, signing the informed consent form, the participants are selected as subjects by reviewing the selection criteria and exclusion criteria in accordance with the clinical trial plan. Selected subjects will fill in the demographic surveys, case medical history, physical examination, clinical pathology examination pregnancy test, single chest x-ray, ECG test, and will be assigned randomly into the test group or the active comparator group according to precompleted random templates, and after assigning a registration number, clinical trial will be conducted at the scheduled time. The subject identification codes will be recorded in the following manner:

Provider Code: Wonkwang University Sanbon Hospital (WS)Agency Code – Test Year - Test Serial Number - Registered Order

(ex: WS-18-01-015: 15th registered patient in Wonkwang University Sanbon Hospital 1st clinical trial in 2018).

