### Eligibility criteria: exclusion criteria

2.5

1.Individuals who demonstrate arrhythmia on EKG, or whose pulse rate per minute is outside of the range of 50 to 1002.Individuals who have a severe physical illness or are medically unstable (as determined by the clinical trial conductor or another medical expert)3.Individuals who have a congenital illness, psychological illness, central nervous problem, peripheral nervous problem, endocrinal illness, immunological disease, basal heart disease, liver disease, or renal disease4.Individuals who have a neurological illness (eg, head trauma) or psychological history (eg, major depressive disorder, anxiety disorder, bipolar disorder, or schizophrenia)5.Individuals with an intracardiac pacemaker inserted, or with a device that stimulates the brain, a ventricular peritoneal short circuit, or other artificial device inserted into the head6.Individuals who take medicines that may affect the autonomic nervous system within 1 week before enrollment in the clinical trial (opiates, stimulants, tricyclic antidepressants, benzodiazepines, cardiac drugs such as beta-blockers, or renin-angiotensin-aldosterone system blockers such as angiotensin-converting enzyme inhibitors and angiotensin receptor blockers)7.Individuals who smoke, drink alcohol, or ingest caffeine-containing products, within less than 2 hours before the clinical trial (eg, coffee, coffee milk, black tea, green tea, cocoa, colas/sodas, chocolate, caffeine-containing energy drinks)8.Individuals who are pregnant or breast feeding9.Individuals who participated in another clinical study within the prior 1 month or who are currently participating in other clinical studies10.Individuals who exhibit difficultly participating in this study, as judged by the investigator

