### Subject withdrawal criteria

2.6

1.Violation of the inclusion criteria or fulfillment of the exclusion criteria2.Serious adverse events that impede trial continuation3.Withdrawal of consent by the subject or a legal representative4.Do not receive 3 consecutive mindfulness meditation sessions5.Violation of the clinical trial protocol by the investigator or the subject6.Use of medications or treatments that can affect the results for clinical trial7.Inappropriate progress as judged by the investigator

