## Discussion

3

This protocol was developed to analyze the relationship between brain and heart through RM and SM. There are some limitations to this present study. First, the participating institutions do not represent all clinical institutions in Korea, because this is limited to single institution. Second, because the participant age in this study is limited to the younger generation, it is not possible to generalize, with respect to age-related outcomes. Third, this study may exhibit difficulty in acquiring all of each subject's personal information because the measurement and intervention of the project is performed in 1 day.

However, the data obtained in this study relating to the brain and heart can be used as basic data and reference data for future brain–heart research. In addition, we will expand the potential impact of oriental medical technology evaluation as evidence-based medicine, establish a scientific basis for clinical trials theory based on clinical data, generate a clinical model and quantitative index for the evaluation of meditation therapy, and identify effects of meditation therapy. Finally, this study will be the first to scientifically measure and analyze the brain–heart relationship in Korea. Therefore, the results of this study will help to gain information and build medical systems for enhanced medical intervention in all diseases that are related to brain and heart.

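### Subjects are randomised at screening although exclusion 7 can be settled only at the later session, and withdrawal rule 4 does not fit a design with one meditation stage

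*Protocol article*

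**What the plan says.** Section 2.9.2 (Screening phase) gives the order of events. After consent, "the participants are selected as subjects by reviewing the selection criteria and exclusion criteria in accordance with the clinical trial plan". They then undergo the screening examinations and are allocated to one of the two arms from a list prepared beforehand. Only then does the session follow: "and after assigning a registration number, clinical trial will be conducted at the scheduled time". Section 2.7.1 agrees: once consent is signed and the inclusion criteria are met, the research coordinator "will sequentially allocate the participant to the treatment or control group according to the random number".

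The session itself is in section 2.9.3. It has three 20-minute stages. The baseline questionnaires and first recordings belong to stage 1, the arms receive their different meditations in stage 2, and stage 3 is again a resting state.

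Exclusion 7 in section 2.5 rules out anyone who smokes, drinks alcohol or takes caffeine "within less than 2 hours before the clinical trial". The first withdrawal ground in section 2.6 is "Violation of the inclusion criteria or fulfillment of the exclusion criteria". The fourth is "Do not receive 3 consecutive mindfulness meditation sessions". Section 2.8 limits blinding to the participants. The Discussion (section 3) notes that "the measurement and intervention of the project is performed in 1 day".

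**The concern.** Eligibility should be settled before allocation wherever it can be. Here one criterion depends on what the subject did in the two hours before the session, while allocation was made earlier, at screening. Someone who has had a coffee on the way to the hospital is therefore already randomised when the breach comes to light, and rule 1 makes that breach a ground for withdrawal.

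Two things are at stake. First, whether to ask, record and act on a breach is then decided after the allocation has been made, by staff who may know it. If enforcement differed by arm, and if withdrawn subjects were left out of the analysis, the comparison would no longer be between the groups as randomised. Second, each such withdrawal uses up a randomised place in a trial of 50.

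Rule 4 raises a different matter. It presupposes a course of several sessions, which this trial does not have.

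**Working it through.** **Order of events, from the article**

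| Step | Section | Relative to allocation |
|---|---|---|
| Consent, eligibility review, screening tests | 2.9.2 | before |
| Random assignment, registration number | 2.9.2, 2.7.1 | – |
| Two-hour window of exclusion 7 closes | 2.5 | after |
| Stage 1: baseline questionnaires, qEEG, HRV | 2.9.3 | after |
| Stage 2: the arms first differ | 2.9.3 | after |

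The two-hour window ends when the session starts, and the session follows allocation. A review at screening therefore cannot settle exclusion 7, and the text describes no second check before allocation. The problem is essentially confined to this item: the ECG and the pregnancy test are listed before assignment, and the medication criterion is tied to enrolment.

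**Who may know the arm.** The coordinator makes the allocation and completes the assignment table (2.7.1). Practitioners cannot be blinded, and only participants are (2.8). The article does not say who judges exclusion 7 on the day, so the most that can be said is that this person may know the arm.

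**The plan's own sample size.** Inputs from section 2.13: standardised effect 1.0, 46 evaluable, 10% dropout, 50 recruited. Assumptions: two-sided 5% level, and the 90% figure read as power. The two-sample t test (noncentral t) needs n = 22.02 per arm, rounded up to 23, so 2 × 23 = 46. The stated figure is reproduced, with power 0.912 at 46.

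**Effect of withdrawals on power.** The rate of exclusion-7 breaches is not given. Let x be the share withdrawn for it on top of 10% dropout, taken over an assumed range of 0 to 20%. Evaluable N = 50 × 0.90 × (1 − x):

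| x | Evaluable N | Power |
|---|---|---|
| 0% | 45.0 | 0.906 |
| 5% | 42.8 | 0.891 |
| 10% | 40.5 | 0.873 |
| 20% | 36.0 | 0.830 |

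**Effect on the type I error if withdrawn subjects are left out.** Simulation with no true effect, 25 per arm, two-sided 5% t test, three subjects removed from one arm only:

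- removal unrelated to the outcome: rejection rate 5.0%
- removal on a trait correlated 0.3 with the outcome: 5.6%

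A pre-session breach by a blinded participant resembles these cases, because it occurs before any outcome exists. The correlation of 0.3 is an assumption.

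**Rule 4 against the design.** Section 2.9.3 has one meditation stage; stages 1 and 3 are resting states, so the three stages cannot be read as three sessions. The Discussion puts measurement and intervention in one day. If rule 4 means not having received three consecutive sessions, every subject meets it. If it means having missed three in a row, nobody can. On neither reading can it operate.

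**The case against.** The strongest reply is that the harm is not in the text. Section 2.6 lists grounds for withdrawal; nowhere does the article say that withdrawn subjects leave the analysis. The analysis set is commonly defined in an SAP, which is not shown. The interval between allocation and session is not stated and may be short. Table 1 and the figures, which carry the schedule, are not reproduced and could show a check on arrival. These points stand: bias is a possibility, not an established fact. They do not change the order that sections 2.9.2 and 2.7.1 state in words.

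Several stronger readings are tempting and are not supported:

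- **A large inflation of the error rate.** Removing the three lowest outcomes of 25 from one arm shifts its mean by about 0.22 SD and raises a 5% error to about 13%. That models removal by outcome, in one arm only, not a breach before stage 1. It could arise only through the investigator-judgement ground in section 2.6, which acts after allocation whenever allocation is made.
- **An underpowered trial.** Five losses among 50 leave 45, one below the stated 46, but power is still 0.906.
- **A baseline coloured by knowledge of the arm.** Participants are blind and complete the questionnaires themselves; qEEG and Holter are instrument recordings. Randomising before baseline is not in itself an error.
- **No concealment of the next allocation.** The article has an independent statistician prepare a blocked table and a trial manager handle the numbers. It does not say whether the coordinator can see future entries, and a condensed article may omit this.

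Finally, recruitment was due to end on 31 October 2018, five days after publication on 26 October, so few subjects could benefit. That limits the value of the change but does not make the order sound.

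**Conclusion.** The point holds in a limited form. As written, one eligibility criterion is settled after allocation, which turns an avoidable screen failure into a post-randomisation withdrawal. This is a cheap improvement to make, not a fatal flaw. Any bias depends on two things the article does not state: whether withdrawn subjects are left out of the analysis, and whether the criterion is enforced differently by arm. The cost in power is modest over the assumed range (0.906 down to 0.830 at 20% extra loss, given effect size 1.0 and a two-sided 5% test).

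The rule 4 contradiction needs no assumption. The rule is wrong as written for a design with one meditation stage in one day.

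**What to change.** Amend sections 2.7.1 and 2.9.2 so that, for subjects not yet randomised, exclusion 7 is confirmed and the stage-1 baseline completed before the allocation is revealed, just before stage 2. Breaches then become screen failures. State that all randomised subjects, including those already enrolled, are analysed in their allocated arm as far as data exist.

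The cost is a short amendment and a small logistic step between stages 1 and 2. The required 46 evaluable subjects do not change, and no extra staff are needed.

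Separately, reconcile withdrawal rule 4 in section 2.6 with the single meditation stage in section 2.9.3 and the one-day conduct described in section 3. What the rule should be is for the sponsor and investigators to decide.
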